## Abstract

**Background:**

Multiple studies have demonstrated the importance of adequate catheter–tissue contact in the creation of effective lesions during radiofrequency catheter ablation. The development of contact force (CF)-sensing catheters has contributed significantly to improve clinical outcomes in atrial fibrillation. However, CF-sensing technology is not used in the ablation of paroxysmal supraventricular tachycardia (PSVT). The possible reason for this is that PSVT ablation with the conventional approach (i.e. nonirrigated, non-CF-sensing catheters) is considered a relatively low-risk procedure with fairly high success rates (short and long term). The aim of this study is to determine whether CF sensing can further improve the outcomes of PSVT ablation.

**Methods/design:**

The COBRA-PATH study is a single-center, two-armed, randomized controlled trial. Patients without structural heart disease being referred for electrophysiology study, because of PSVT and potential treatment with radiofrequency (RF) catheter ablation, will be randomly assigned to either manual ablation with standard nonirrigated ablation catheters or manual ablation with an open-irrigated ablation catheter equipped with CF sensing (used in a virtual nonirrigated modus). The primary study endpoint is the difference in the number of RF applications during the ablation of atrioventricular nodal re-entry tachycardia, and that of Wolff–Parkinson–White syndrome and atrioventricular re-entrant tachycardia. Secondary outcome parameters include acute and long-term procedural success rates, overall duration of RF applications, procedure/fluoroscopy durations and safety parameters.

**Discussion:**

We expect to see a reduced number/duration of RF applications required to achieve effective lesion creation, and consequently a decrease in total procedure/fluoroscopy times. Although a significant improvement in procedural success rates (acute/long term) might not be feasible to demonstrate (given the relatively high success rate of the standard ablation method), the possible decrease in procedure duration and the consequential reduction of radiation exposure has important clinical implications for both operators and patients undergoing the procedure.

**Trial registration:**

ClinicalTrials, NCT04078685. Retrospectively registered on 2 September 2019.

## Background

Contact force (CF) is a relatively new technology that provides real-time feedback on catheter–tissue contact during radiofrequency (RF) ablation. There is compelling evidence that CF between the tip of the catheter and the target tissue within the cardiac chamber is a key factor for safe and effective lesion creation. Insufficient CF leads to ineffective lesion formation whereas excessive CF may result in procedural complications. Before the development of CF-sensing ablation catheters, operators could only rely on surrogate indicators of tissue contact, such as tactile feedback, intracardiac electrograms, baseline impedance, impedance change, electrode temperature and catheter location by fluoroscopy or electroanatomic mapping. These measures were less accurate and did not provide instant feedback on contact [1–3].

Since the introduction of CF-sensing catheter ablation therapy, many studies have demonstrated the importance of this novel technology in the field of atrial fibrillation ablation, as presented in Table 1 [1, 4–19]. These investigations demonstrated that CF-sensing improves the recurrence rate, significantly reducing the total procedure, ablation times and fluoroscopy times in comparison with conventional therapy. Moreover, based on the findings of these clinical trials, important CF parameters have been determined and introduced into clinical practice guidelines for atrial fibrillation ablation, such as minimum CF, target CF, minimum force–time integral (FTI), continuity index (CI) and lesion-size index (LSI) [7, 17, 19].

**Table 1 Tab1:** Clinical studies on catheter ablations with contact force (CF)-sensing catheters in patients with atrial fibrillation

Study	Year	Type of study	Number of patients		Follow-up (months)	Ablation	CF catheter
			CF	Control			
Martinek et al. [4]	2012	Prospective nonrandomized study	25	25	n/a	Circumferential PVI	ThermoCool SmartTouch
Kuck et al. [5] (TOCCATA)	2012	Prospective nonrandomized study	72	n/a	12	Circumferential PVI Right-sided SVT ablation	TactiCath
Reddy et al. [6] (TOCCATA)	2012	Prospective nonrandomized study	32	n/a	12	Circumferential PVI	TactiCath
Neuzil et al. [7] (EFFICAS I)	2013	Prospective nonrandomized study	46	n/a	3	Circumferential PVI plus remapping at 3 months	TactiCath
Casella et al. [8]	2014	Randomized controlled trial	20	35	12	Circumferential PVI	TactiCath or Contact Therapy Cool Path
Andrade et al. [9]	2014	Prospective nonrandomized study	25	50	13.3	Circumferential PVI	ThermoCool SmartTouch
Kimura et al. [10]	2014	Randomized controlled trial	19	19	6.7	Circumferential PVI	ThermoCool SmartTouch
Marijon et al. [11]	2014	Prospective nonrandomized study	30	30	12	Circumferential PVI	ThermoCool SmartTouch
Natale et al. [12] (SMART AF)	2014	Prospective nonrandomized study	161	n/a	6	Circumferential PVI plus possible linear ablations and CFAE. CTI line if patient with AFL	ThermoCool SmartTouch
Sciarra et al. [13]	2014	Prospective nonrandomized study	21	21	2.5	Circumferential PVI	ThermoCool SmartTouch
Wakili et al. [14]	2014	Prospective nonrandomized study	32	35	12	Circumferential PVI	TactiCath
Wutzler et al. [15]	2014	Prospective nonrandomized study	31	112	12	Circumferential PVI	TactiCath
Jarman et al. [16]	2015	Retrospective case–control study	200	400	11.4	PVI^a^	ThermoCool SmartTouch
Ullah et al. [1]	2014	Prospective nonrandomized study	50	50	12	PVI or WACA plus CTI plus mitral isthmus plus roof line^b^	ThermoCool SmartTouch
Kautzner et al. [17] (EFFICAS II)	2015	Prospective nonrandomized study	24	26 patients from EFFICAS I	3	Circumferential PVI plus remapping at 3 months	TactiCath
Sigmund et al. [18]	2015	Prospective case-matched control trial	99	99	12	Circumferential PVI plus linear ablation plus CFAE^c^	ThermoCool SmartTouch
Reddy et al. [19] (TOCCA-STAR)	2015	Randomized controlled trial	146	134	12	Circumferential PVI plus possible linear ablations and CFAE. CTI line if patient with AFL	TactiCath

^a^For paroxysmal atrial fibrillation (AF), additional linear ablation was performed only exceptionally; nonparoxysmal AF, use of additional lesions varied by operator, including linear lesions at the roof, mitral isthmus, posterior wall and CTI, targeting of complex fractionated electrograms, and ablation at the endocardial and epicardial aspects of the coronary sinus

^b^CTI line added in patients with AFL hx; if remained in AF, linear lesions added at mitral isthmus and roof, both point-to-point and drag

^c^PVI only, PVI with lines, PVI with lines and CFAE, and PVI with CFAE

*AFL* atrial flutter, *hx* history *n/a* not applicable, *PVI* pulmonary vein isolation, *SVT* supraventricular tachycardia, *CTI* cavotricuspid isthmus isolation, *CFAE* Complex Fractionated Atrial Electrograms, *WACA* wide antral circumferential ablation

Despite compelling evidence in atrial fibrillation ablation, no randomized controlled clinical trial has yet assessed the feasibility of CF sensing in the ablation of (paroxysmal) supraventricular tachycardia ((P)SVT). The relatively high success rate of SVT ablations using the conventional (non-CF-based) methodology might have contributed to this virtual ignorance of CF sensing for these procedures. The acute success rates of catheter ablation of atrioventricular nodal re-entry tachycardia (AVNRT) and of accessory pathway ablations (i.e. Wolff–Parkinson–White syndrome–atrioventricular re-entry tachycardia; WPW-AVRT) with the conventional (non-CF-based) approach has been reported to be 96–97% and 93% respectively, whereas the recurrence rate of AVNRT ablation is approximately 5% and that of WPW-AVRT ablation is around 8% [20–25]. Furthermore, in contrast to atrial fibrillation ablation, the ablation target in (P)SVT usually comprises a much smaller area of myocardial tissue (slow pathway, accessory pathways, cavotricuspid isthmus or an atrial focus). Another more practical reason for the virtual ignorance of CF sensing in (P)SVT might be the nonavailability of CF-sensing technology in conventional nonirrigated ablation catheters.

The aim of this randomized controlled trial (RCT) is to demonstrate the superiority of the CF-sensing-based approach compared to the conventional (non-CF-sensing) approach in the catheter ablation of PSVTs by assessing the improvement in the number of RF applications, and to prove the safety of the open-irrigated, CF-sensing ablation catheters.

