### Primary and secondary outcome parameters

The primary outcome of this study is the number of radiofrequency ablations during the ablation procedures of AVNRT and WPW-AVRT. The secondary outcome parameters are overall duration of radiofrequency applications, acute procedural success/failure, fluoroscopy time, total procedural duration, (serious) adverse events and long-term procedural success. The following additional characteristics and parameters are collected and investigated during the study: baseline demographic characteristics of patients, previous antiarrhythmic drug treatment, history of cardiac arrhythmias (first onset of PSVT, and other possible associated arrhythmias, e.g. atrial fibrillation, atrial flutter, premature ventricular contraction, (non)-sustained VT) and prior ablation history.

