### Statistical analysis

The number of radiofrequency applications during the ablation procedures of AVNRT and WPW-AVRT (primary study endpoints), as well as other continuous procedural parameters from the group of secondary study endpoints (such as total procedural duration, fluoroscopy time and overall duration of RF applications), will be expressed as mean ± SD or median (interquartile range) depending on their distributions, and statistical analysis of these variables will be conducted using either the two-sample *t* test or the Mann–Whitney test, again depending on the underlying distribution of the data.

The recurrence rate of PSVT at 1 year (as an indicator of long-term success rate of the index procedure), as well as the acute success rate and the major/minor complication rates of the index procedures (secondary study endpoints), will be presented as absolute and relative frequencies. The associations between treatment and these secondary endpoints will be analyzed with the chi-squared test or with Fischer’s exact test, as appropriate. Moreover, logistic regression will be performed to examine these associations and will, if needed, be adjusted for unbalanced baseline characteristics. Freedom from PSVT recurrence will be determined with Kaplan–Meier analysis, and differences in recurrence-free survival rates will be evaluated with the log-rank test. A *p* value of 0.05 will be considered significant for all statistical determinations, and all reported *p*-values will be based on two-sided tests.

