### Sample size calculation

The sample size calculations were based on the following:
A retrospective analysis of AVNRT/WPW-AVRT ablations performed in our institute within the last 6 months revealed that the mean number of radiofrequency applications required for successful ablations was 4.81 ± 3.21, which is in line with previous results found in the literature [30].According to previous studies, the ablation efficiency for patients with atrial fibrillation has been increased with the use of CF-sensing technology by approximately 15–20% [1, 4–19], as revealed by the reduced number and duration of RF applications in atrial fibrillation ablation. We assume that in terms of ablation efficiency, the significance of CF sensing will be even more pronounced in the treatment (catheter ablation) of such simple arrhythmia substrates as that of AVNRT and WPW-AVRT, therefore (regarding our sample calculations) a 25% reduction in RF application number was considered realistic to represent a clinically significant change.

Evaluation of the distribution of RF applications in our database of AVNRT/WPW-AVRT ablations (mentioned under the first point) revealed a positive skewness, and therefore logarithm transformation (natural log) was performed in order to approximate a normal distribution of the variables. The mean and standard deviation of the natural logs of application numbers were computed and amounted to 1.39 ± 0.59; these values were subsequently used in our sample size calculations.

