For the sample size calculations, we used two different calculator tools: an online sample-size calculator tool (http://powerandsamplesize.com/Calculators/Compare-2-Means/2-Sample-Equality) and G*power (http://www.gpower.hhu.de/en.html). In both methods, we applied the appropriate test comparing the difference of two independent means of two groups (calculation formulas are presented on the calculator’s website and in G*power). The mean application number of the group with the study catheter was assumed to be reduced by 25% (as already mentioned) compared to the control group (thus amounting to 1.39 × 0.75 = 1.043) and the standard deviation of this group was assumed to be identical to the control group. The power was set to 80% and the type 1 error (α) to 5% (two-tailed). Using these parameters, both methods/calculators determined the same sample size of patients (2 × 46 = 92), which would be required to show a statistical significance in the case of a clinically significant reduction (25%, as mentioned earlier) of RF application number.

Allowing a dropout rate of 15%, the total sample size would become around 106. In addition, the acute success rate of AVNRT/WPW-AVRT ablations has been reported to be around 95% [26, 29]. Taking this into consideration, the total number of patients required for the purposes of this study would be 112.

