A recent meta-analysis of the controlled trials on CF-based ablation vs. conventional approach in patients with atrial fibrillation (presented in Table 1) has found enhanced safety of using CF-based ablation technology with acceptable rates of minor and major complications and reduced rates of cardiac perforation (although this did not reach statistical significance) [3]. This is probably attributable to two factors: the continuous monitoring of the catheter while manipulating the cardiac chambers, with real-time feedback of catheter tip–tissue contact; and avoiding ablation when the CF is suboptimal (which would reduce the need for excessive ablations and subsequent related complications). We strongly believe that through these two factors, CF sensing would have a similar beneficial effect on the complication rate of AVNRT/accessory pathway ablation. Therefore (based on the aforementioned studies), as far as potential risks associated with CF sensing are concerned, we believe that there is no additional risks of complications expected with the use of CF sensing during AVNRT/accessory pathway ablation. Instead, using CF sensing should rather reduce the complication rate and enhance the safety profile of these ablations, as well.

Despite compelling evidence in atrial fibrillation ablation, no randomized controlled clinical trial has yet assessed the feasibility of CF sensing in the ablation of (P)SVTs. Although the TOCCATA study enrolled patients with right-sided SVTs as well, it was conducted in a nonrandomized, uncontrolled fashion, comparing the results of CF-sensing-based catheter ablations (performed in this study with the TactiCath catheter) with the results of conventional (non-CF-sensing-based) ablation techniques reported in the literature (for right-sided SVT) prior to the study. In addition, the focus of this trial was the safety profile of the CF-sensing catheter, and parameters such as the recurrence rate, total procedure/ablation time and fluoroscopy time have not been evaluated for right-sided SVTs [5, 6].

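### The Background sets out to prove the safety of the contact-force catheter, but tests of a difference and a sample sized only on RF application number cannot establish it

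*Protocol article*

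**What the plan says.** The last paragraph of the Background gives two aims: superiority of the contact-force approach on the number of RF applications, and "to prove the safety of the open-irrigated, CF-sensing ablation catheters".

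The section on primary and secondary outcome parameters places safety among the secondary outcomes: "total procedural duration, (serious) adverse events and long-term procedural success".

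Under Statistical analysis, major and minor complication rates are to be shown as absolute and relative frequencies. The comparison between arms "will be analyzed with the chi-squared test or with Fischer’s exact test, as appropriate", with logistic regression in addition. A "value of 0.05 will be considered significant for all statistical determinations", and all tests are two-sided. The section attaches no non-inferiority margin, acceptable complication rate or confidence-interval criterion to safety.

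The Sample size calculation uses only the natural log of the number of RF applications, whose mean and SD "amounted to 1.39 ± 0.59". It leads to 92 evaluable patients and, after inflation, 112.

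The abstract concedes that better success rates may not be demonstrable. No matching statement is made for complications. The Discussion instead records an expectation: "we believe that there is no additional risks of complications expected with the use of CF sensing".

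**The concern.** To prove safety is a confirmatory claim: the data must rule out an excess of harm larger than some stated amount. A chi-squared or Fisher test asks the opposite question, namely whether a difference can be shown. When events are rare and the arms small, failing to show a difference is the likely result whether or not the new catheter does more harm. The stated aim therefore asks for something that the stated analysis and sample size cannot give.

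The safety question is a genuine one for this trial. The reassurance cited comes from ablation of other arrhythmias, whereas here an irrigated catheter is run at very low flow, and the Limitations section itself says that the residual irrigation may affect outcome.

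**Working it through.** **1. Number per arm.** Inputs from Sample size calculation: log-scale control mean 1.39, SD 0.59, a 25% reduction (difference 1.39 × 0.25 = 0.3475), two-sided α 5%, power 80%.

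- n per arm = 2 × (1.960 + 0.842)² × 0.59² / 0.3475² = 45.3, rounded up to 46; total 92, as stated.
- 92 × 1.15 = 105.8, about 106; 106 / 0.95 = 111.6, about 112, as stated.
- With 1:1 allocation this is 56 enrolled per arm. The evaluable number could be as low as 46.

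No complication rate, margin or precision target enters this calculation.

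**2. What zero events would show.** With 0 events in n patients, the exact upper limit is 1 − 0.025^(1/n) for a two-sided 95% interval and 1 − 0.05^(1/n) for a one-sided 95% bound.

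| n in the contact-force arm | Two-sided 95% upper limit | One-sided 95% upper limit |
|---|---|---|
| 56 | 6.4% | 5.2% |
| 46 | 7.7% | 6.3% |

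If the true rate were 2% (assumed), the chance of seeing no event in 56 patients would be 0.98^56 = 32%.

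**3. What the planned test could detect.** The article gives no complication rates, so all rates here are assumptions over a range. Power of the two-sided Fisher test at 0.05, by exact enumeration of both binomial distributions with 56 per arm:

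| Control rate vs contact-force rate (assumed) | Power |
|---|---|
| 2% vs 4% | 0.8% |
| 2% vs 6% | 4.5% |
| 2% vs 8% | 12.5% |
| 2% vs 10% | 24% |
| 5% vs 10% | 8% |
| 5% vs 15% | 29% |
| 5% vs 20% | 58% |
| 10% vs 30% | 69% |

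In terms of counts, 5 events against 0 gives p = 0.057 and 7 against 1 gives p = 0.061. The smallest significant split against zero is 6 against 0 (p = 0.027).

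**4. Would a margin rescue the aim at this size?** For equal true rates p, one-sided 2.5% and 80% power, n per arm = 2p(1 − p) × (1.960 + 0.842)² / margin².

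- Margin of 5 percentage points: 63, 124, 183 and 299 per arm at p = 1%, 2%, 3% and 5%.
- Margin of 10 points: 16, 31, 46 and 75 per arm at the same rates.

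At 56 per arm a 5-point margin would have 76%, 47%, 34% and 23% power at those rates. Of the two margins, only the 10-point one reaches 80% power, and only at rates of 1% to 3%. These margins are illustrations; the article names none.

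**The case against.** The case against is reasonable in several respects.

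- The wording about proof occurs in one Background sentence. The abstract's aim does not mention it, the outcome list treats adverse events as secondary, and the section on excluding enrolled patients from follow-up speaks only of assessing safety. Secondary safety outcomes are usually underpowered, and sizing a trial on its primary endpoint is not an error. This stands, and it is why the remedy is to reword the aim rather than to enlarge the trial.
- Per-arm frequencies are already planned, so part of the remedy is in place. This also stands.
- Low power is not universal. Minor complications are defined broadly and may be commoner, and large differences in commoner events would be found more often than not (58% to 69% above). It would be too broad to say that nearly every result must be non-significant; the very low power applies to rare major events.
- Confidence intervals and rules of interpretation may sit in a full protocol or analysis plan that is not shown. Their absence from an article would not be a finding by itself. The point rests on what is printed: an aim of proof, tests of a difference, and a sample size that takes no account of complications.

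A reader might go further and infer that a non-significant p-value will be presented as proof of safety. The article does not support that. It contains no rule that p above 0.05 establishes safety, and the Discussion sentence on risk is a prior expectation drawn from atrial fibrillation studies, not a criterion of analysis.

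**Conclusion.** The mismatch is real. The Background claims a proof of safety that the planned comparison and about 56 patients per arm cannot deliver, and the article states no limitation for complications as its abstract does for success rates. For rare major events, even a result with no events at all leaves rates up to 6.4% compatible with the data, and a tripling from 2% to 6% would be detected about 5% of the time.

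The upper limit rests only on the number per arm and would be 7.7% with 46 evaluable. The power figures rest on assumed rates and rise materially only for large differences in commoner events. The primary endpoint and its sample size are untouched. The point concerns what the trial may conclude about safety, not how the authors will report it.

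**What to change.** 1. In the Background, restate the second aim as describing or estimating the safety of the contact-force catheter.
2. In Statistical analysis, add exact 95% confidence intervals to the per-arm complication frequencies already planned, and a 95% confidence interval for the risk difference, for major and minor events separately.
3. State that a non-significant test on complications will not be taken as evidence of safety or equivalence, and add to the Limitations that the trial was not sized for complications.

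If a confirmatory safety claim is wanted instead, a justified margin would have to be fixed in advance and the trial sized for it. With the 5-point margin used for illustration, that means 63 to 299 per arm at assumed rates of 1% to 5%.

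The first route costs a few sentences and no additional patients, procedures or data. Its downside is a less favourable safety claim.
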